## Methods and design

This is a randomized, non-pharmacological, single-center, cross-over study. Duration of the study: 24 months. The study takes place in the Neonatal Intensive Care Unit.

This study aims at recruiting about twenty very low birth weight infants, either IUGR or NON-IUGR.

### Inclusion criteria

· Weight at birth ranging: 700–1501 grams;

· Gestational age up to 25 weeks and 6 days;

· Written informed consent from parents or guardians.

### Exclusion criteria

· Major congenital abnormalities (severe heart or cerebral disease, chromosomopathies, severe renal malformations, any malformation or disease of the gastroenteric tract)

· Patients enrolled in other trials

· Significant multi-organ failure prior to trial entry (perinatal asphyxia with renal, cardiac or cerebral impairment, DIC)

· Pre-existing cutaneous disease not allowing the placement of the probe

### Eligibility to randomization

Infants who fulfill the following requirements are eligible to randomization:

· achievement of at least 100 mL/Kg/day of enteral nutrition

· adequate ventilation i.e. infants who are not intubated and not in-cPAP with a FiO2≥50% at the achievement of 100 mL/Kg/day of enteral nutrition;

· no NEC;

· Written informed consent from parents or guardians.

#### Stratification

Randomization will be stratified in two groups: IUGR infants (approximately 10 children) and NON-IUGR infants (approximately 10 children).

At the achievement of an enteral intake of 100 mL/Kg/day the patients (IUGR and NON IUGR separately) will be randomized in 2 groups: Group A (n=10) will start with bolus administration of nutrition (in 10 minutes); then, after at least 3 hours, they will be fed by the same amount of feed administered as continuous nutrition for 3 hours; Group B (n=10) will start with continuous administration of nutrition for 3 hours followed by a bolus administration of the same amount of feed (in 10 minutes) after at least 3 hours.

The infants of the Group A will be fed with continuous nutrition until the achievement of full enteral feeding (enteral intake of 160 mL/Kg). The infants of the Group B will be fed with 7 or 8 boli/d until the achievement of full enteral feeding.

If, due to clinical instability (i.e. desaturation episodes or bradicardia) during the feeding, a change occurs in the modality of feeding, the results will be analyzed according to the “intention to treat” or the “by treatment” analysis.

All the patients will undergo a baseline evaluation in the first 72 hours of life including: cerebral ultrasound, cardiac ultrasound and abdominal ultrasound.

After birth, in the first 24 hours of life, and in the transitional period, between the 48^th^ and 72^nd^ hours of life, all infants’ intestinal perfusion will be evaluated with NIRS and the echocolordoppler (evaluation of the superior mesenteric artery blood flow) will be performed. The evaluations with NIRS and with the echocolordoppler will be performed under condition of clinical stability (absence of arterial desaturation or instability of cardiocirculatory parameters). Data from NIRS will be collected for 3 hours. Other anamnestic and clinical data will be collected (gestational age, umbilical arterial pH, race, obstetrical anamnesis, mode of delivery, umbilical arterial and venous catheters, patent ductus arteriosus, respiratory distress syndrome, mechanical ventilation, episodes of clinical sepsis). All the infants will be at nothing per os (npo) at the moment of the first two evaluations.

According to our protocol enteral nutrition will start after the 72^nd^ hour of life as minimal enteral feeding (MEF), intake less than 20 mL/Kg/day of enteral feeding will be administered. The increase will be by 20 mL/Kg/day if enteral nutrition is well tolerated. All the infants, according to our standardized protocol, will start parenteral nutrition on the first day of life. The infants will be fed with human milk, if available, (human milk will be fortified at an achievement of an enteral intake of 100 ml/Kg/d), or with a preterm formula (75–80 Kcal/100 mL). The nutrition will be administered via the nasogastric route.

On the randomization day intestinal and cerebral regional oximetry will be measured via near infrared spectroscopy (NIRS) (INVOS- 5100 C) sensors placed over the abdomen (splanchnic bed) and on the forehead (cerebral bed). Recording of the tissues oximetry will start 30 minutes before the feed and will stop 30 minutes after the end of the nutrition. Intestinal and celebral oximetry will be measured before the feed (B_0_) and 30 minutes after the feed (B_1_) by bolus; during the continuous nutrition the measurements will be performed before (C_0_), 30 minutes from the start of the nutrition (C_1_) and 30 minutes after the end of the gavage (C_2_).

The TOI will be obtained simultaneously at the two locations. The TOI measurement recordings will be obtained for 3 minutes from both the head and the abdomen. Those measurements will be combined as a ratio of abdominal TOI over brain TOI to produce a CSOR (TOI_abdomen_/TOI_brain_). Arterial haemoglobin oxygen saturation, measured by pulse oximetry, will be recorded during the NIRS tracing. NIRS tracing will be used only in the absence of desaturation (< 85% arterial saturation).

Capillar haemoglobin concentration will be measured on the day of the evaluation.

An evaluation of blood flow velocity of the superior mesenteric artery (peak sistolic and end-diastolic velocity, mean velocity, and pulsatility index) will be performed meanwhile. To achieve imaging of the SMA the transducer will be placed on the mid-abdomen above the umbilicus. The SMA will be identified at its emergency from the aorta and sample volume will be placed a few millimetres from its origin. Neonatologists with the same expertise and manual ability will perform the ecocholordoppler evaluations. The evaluations and the measurements will be performed on 5 contiguous homogeneous waves.

Measurements of body weight, length and head circumference will be performed at predefined times: at birth, at the beginning of MEF, on the randomization day, at the achievement of full enteral feeding, at 28 days of life and at 36 weeks of gestational age.

Parameters of feeding tolerance are those routinary used in the NICU (maximum gastric residual and residual appearance). The enteral nutrition will be discontinued or carried on according to our feeding protocol.

The follow-up will end at the achievement of a full enteral feeding, enteral intake of 160 mL/Kg/die or at 28 days of life, whichever occurs later. Patients may drop-out before this intended end because of the following withdrawal causes:

Withdrawal of the consent by the relatives

Severe skin reaction due to the skin probe

Transferral to another hospital

Death

After study end, patients will be fed according to the standard protocol of our Unit.

During the study, recommended diagnostic and therapeutic procedures are those usually performed as standard care in our Unit.

No new special measure for safety is planned since all the diagnostic and therapeutic procedures are part of the standard approach to the VLBW infant in our Unit.

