The primary end-point analysis as well as all secondary analyses regarding randomized patients will be based on the ITT (intention-to-treat) principle. Comparisons of the two arms accounting for deviations from the assigned arm (analyses by “performed treatment”) will also be added to this main analysis. The primary endpoint will be analyzed with a two-tailed matched pairs t-test, after checking of appropriateness of assumptions. In particular, checking will concern the normality assumption, since period effect and cross-over effect appear both very unlikely in this study. Should normality be not adequate, non-parametric test such as the Wilcoxon signed ranks test will be applied [20]. An appropriate generalized linear model will be used to investigate the relationship between the CSOR cross-over difference and the candidate covariates. Should any raw CSOR observations be missing (e.g. NIRS instrument failed to measure or to save measurements), their estimation via imputation or other appropriate methods will be taken into account. The comparison of growth variables by randomized arm will be performed with either the two-tailed t-test or a non-parametric alternative (e.g. Mann–Whitney test), should the normality assumption be not reasonable. The time from randomization till achievement of the full enteral feeding will be analysed with the Kaplan-Meier estimator, in which full enteral feeding as defined in the protocol will be considered as the sole ‘event’, while censoring will occur for withdrawal for any cause. Standard errors will be computed according to Greenwood formula and the log-rank test will be used for univariate comparisons.

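### A severe probe skin reaction may end follow-up of a randomised infant, although the remaining feeding and growth outcomes need no probe

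*Protocol article*

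**What the plan says.** The follow-up text (Methods and design, under Stratification) sets the end of follow-up at "enteral intake of 160 mL/Kg/die or at 28 days of life, whichever occurs later". It continues: "Patients may drop-out before this intended end because of the following withdrawal causes". Four causes follow: withdrawal of consent, "Severe skin reaction due to the skin probe", transfer to another hospital, and death. The list does not distinguish an infant in whom NIRS is stopped from an infant who leaves follow-up.

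In the Kaplan-Meier analysis of time to full enteral feeding (Statistical analysis), full feeding is the only event, "while censoring will occur for withdrawal for any cause". The same section says that the primary analysis "as well as all secondary analyses regarding randomized patients will be based on the ITT" principle.

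NIRS is scheduled in the first 24 hours, at 48 to 72 hours, during minimal enteral feeding (Abstract) and on the randomization day. For that last day the text says "Recording of the tissues oximetry will start 30 minutes before the feed and will stop 30 minutes after the end of the nutrition". No later recording is scheduled. Anthropometry after randomization is due "at the achievement of full enteral feeding, at 28 days of life and at 36 weeks of gestational age".

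**The concern.** The skin reaction differs in kind from the other three causes. After death, transfer or withdrawn consent, the unit can no longer collect the data. After a skin reaction the infant is still in the unit, still on the assigned regimen and still being weighed and measured. What the reaction may prevent is another probe recording, and after the randomization day none is planned.

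As written, the list permits a problem with the measuring device to end observation of outcomes that do not use the device. In a trial of about 20 infants every randomised infant counts in the by-arm comparisons, which are time to full enteral feeding and growth. The loss would be avoidable.

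**Working it through.** **Inputs from the protocol article**

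- Randomization at an enteral intake of 100 mL/kg/day (Eligibility to randomization).
- Full enteral feeding at 160 mL/kg/day (Endpoints; Statistical analysis).
- Planned increase of 20 mL/kg/day if tolerated (Methods and design).
- About 20 infants, 10 per group (Stratification; Sample size).
- Main growth comparison from randomization to full enteral feeding (Endpoints; Statistical analysis).
- Rate of severe skin reactions: not given. One to three infants is used below as an assumption, for scale only.

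**1. The plan's own figure.** Table 1 gives power of 84%, 80% and 78%. The check is a paired t-test with n = 20, 19 degrees of freedom, two-sided α = 0.05 and noncentrality (difference/σ) × √20, taking σ as the SD of the within-infant difference:

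| σ | difference | noncentrality | power | Table 1 |
|---|---|---|---|---|
| 0.10 | 0.07 | 3.13 | 84.4% | 84% |
| 0.15 | 0.10 | 2.98 | 80.7% | 80% |
| 0.20 | 0.13 | 2.91 | 78.7% | 78% |

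The table is reproduced. It concerns the primary endpoint and is not at issue here.

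**2. Which outcomes still need the probe after the randomization day**

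| Outcome | Needs NIRS? | Collected when |
|---|---|---|
| CSOR cross-over difference (primary) | Yes | Randomization day only |
| Days to 160 mL/kg/day | No | After randomization |
| Weight, length, head circumference | No | Full feeding and later |

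**3. How much one withdrawal costs in follow-up time.** Time from randomization to full feeding at the planned rate is (160 − 100)/20 = 3 days. It is longer if feeds are not tolerated. An infant censored on day 0 or day 1 normally leaves the risk set before any infant has reached the event, and so adds almost nothing to the log-rank comparison. Its main growth comparison has no second measurement. The imputation provision in Statistical analysis is written for raw CSOR observations, so it does not restore growth data.

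**4. Size**

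- One infant: 1/20 = 5% of the trial and 1/10 = 10% of its arm.
- Three infants (assumed upper end): 3/20 = 15% of the trial.
- Standard error of a two-arm growth difference, relative to 10 versus 10 with equal variances:
  - 10 versus 9: √[(1/10 + 1/9)/(1/10 + 1/10)] = √(0.2111/0.2000) = 1.027, about 3% wider.
  - 10 versus 7 (all three in one arm): √(0.2429/0.2000) = 1.102, about 10% wider.

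**5. Effect on the primary endpoint.** If both test feeds were recorded before the reaction was found, the CSOR difference is already in hand and nothing is lost. If the reaction prevents the second recording, the pair is incomplete because the probe could not be used, and the withdrawal rule is not the cause. Power with 19 complete pairs would be 82.3%, 78.5% and 76.4% in the three scenarios, but the proposed change would not recover that loss.

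**The case against.** The strongest case on the other side is that this is a wording point in a study that describes itself as explorative, and that it invites stronger inferences than the text allows. Much of that stands.

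- **Mandatory withdrawal.** A reader might infer that every reaction ends follow-up. The text says infants *may* drop out, so the loss is permitted and not required. What remains is that the document leaves the choice open and fixes censoring when it is taken.
- **Breach of intention-to-treat.** A reader might see a contradiction. In this protocol the principle is set against deviations from the assigned arm. An infant censored at withdrawal stays in its assigned arm and contributes until then, so censoring alone does not contradict the principle.
- **Selective removal and bias.** A reader might suppose that losing infants with fragile skin distorts the comparison. Both groups receive both test feeds under NIRS on the same day, so planned probe exposure is equal, and nothing in the document links a reaction to the assigned regimen.
- **Lost safety follow-up.** Nothing states that a reaction goes unrecorded or is not followed. The article promises complete safety analyses in the publication, and such detail is commonly left to the full protocol. Silence here is not a finding.
- **Reactions before randomization.** A reader might want these infants randomised all the same. The primary endpoint needs the probe, and the Exclusion criteria already exclude pre-existing skin disease that does not allow its placement. Randomising an infant who cannot be measured would mean imputing the whole primary outcome under a provision whose example is an instrument failing to measure or save readings. The point does not extend to these infants.

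The objection does not explain why an infant already randomised, with no further NIRS scheduled, should be able to leave feeding and growth follow-up because of the probe.

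**Conclusion.** The point holds in a limited form. For infants already randomised, the protocol permits an avoidable loss of secondary-outcome data: the list of withdrawal causes includes an event that does not stop those data being collected, and the analysis section censors whoever leaves. One such withdrawal on or just after the randomization day would remove nearly all of that infant's feeding-time information and its main growth comparison, which is 5% of the trial or 10% of an arm.

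The consequence is lower precision in secondary outcomes. This rests on three assumptions: feeds advance at about the planned rate, the reaction is recognised close to the randomization day, and the option to withdraw is used. With no reaction rate in the document and a low rate likely, the expected numerical effect is small. The change is worth making because it costs almost nothing and every infant matters in a trial of this size.

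**What to change.** In the follow-up text under Methods and design, separate two states: *NIRS measurement stopped* and *withdrawn from follow-up*. Then state that, for a randomised infant, a severe skin reaction alone places the infant in the first state only. It is not a cause of withdrawal or of censoring. Routine feeding and growth data continue to the planned end and are analysed by assigned arm. Adjust the censoring sentence in Statistical analysis to match.

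Leave the handling of infants whose reaction occurs before randomization and prevents CSOR measurement as it is. The change concerns data retention only and says nothing about when a probe should be removed or how an infant should be fed.

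Cost: one sentence in the follow-up text and a matching phrase in the analysis text. The retained outcomes are already scheduled, so no procedure is added, and the planned sample size and Table 1 do not change.

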### Statistical considerations

#### Randomization

Randomized interventions are described in Section ‘Methods and Design’. This section summarizes procedures and methodology, which will be adopted**.**

Patients eligible to randomization: all VLBW infants enrolled and eligible to the study, either IUGR or non-IUGR, who fulfil the following requirements:

1. achievement of 100 mL/kg/day of enteral nutrition;

2. adequate ventilation i.e. infants who are not intubated and not in-cPAP with a FiO2≥50% at the achievement of 100 mL/Kg/day of enteral nutrition;

3. no NEC;

4. Informed consent from parents or guardians.

When to randomize:

a. * After *achievement of 100 mL/kg/day of enteral nutrition in presence of adequate ventilation (see point 2 above)

Modalities of randomization:

b. Logistics: investigators will ask for randomization by access to a specific software which will provide the assigned arm, after check on the eligibility criteria.

c. Methodology: randomization will be stratified (IUGR vs non-IUGR) and by blocks: the random assignment will be produced by an automatic procedure Ranlist [19] and will be based on random permuted blocks of small size, given the limited number of infants expected in each stratum.

**Randomization refusals:** if parents or guardians do not agree with randomization, patients will be excluded from the study and should be fed according to nutrition procedure regarded as the most appropriate for the child based on the Unit standard policy.

#### Statistical analysis

The primary aim of the study is to compare the impact on intestinal perfusion of 2 different nutrition modalities, bolus (BN, Group A) versus a 3-hour nasogastric nutrition (CN, Group B). The impact on intestinal perfusion is defined as the difference between pre- and post-prandial CSOR values measured with NIRS 30 minutes before feeding and at the expected peak after feeding (3 hours in CN and 30 minutes in BN). Pre- and post-prandial CSOR values will be calculated as the mean of 5-minute NIRS evaluations about the intended time-point (e.g. for baseline CSOR measurement, 2.5 minutes before and 2.5 minutes after the 30th minute before start of the randomized feed). Given that the study is a cross-over study, each infant will be evaluated both for CN and BN and the cross-over CSOR difference will be the primary endpoint.

As a secondary analysis, the cross-over difference of CSOR values as well as that of SO2s values (i.e. the splanchnic saturation slope) will be analysed comparing intra-uterine growth (IUGR vs. non-IUGR).

The impact of the 2 nutrition modalities on CSOR will also be studied in a multivariable context, adjusting for factors including the baseline CSOR value, the baseline Doppler flow velocimetry (both measured within the first 72 hours of life) and the intra-uterine growth (IUGR vs. non-IUGR).

Other secondary analyses include:

· Comparison of the time needed to reach full enteral feeding (i.e. days from randomization till enteral intake of 160 mL/Kg/day of formula or human milk) by randomized arm;

· Comparison of growth as measured by weight, length and head circumference by randomized arm. Main comparison will be between measures at randomization and at achievement of full enteral feeding. The growth at 28 days of life will also be compared with the appropriate standard growth curves.

The primary end-point analysis as well as all secondary analyses regarding randomized patients will be based on the ITT (intention-to-treat) principle. Comparisons of the two arms accounting for deviations from the assigned arm (analyses by “performed treatment”) will also be added to this main analysis. The primary endpoint will be analyzed with a two-tailed matched pairs t-test, after checking of appropriateness of assumptions. In particular, checking will concern the normality assumption, since period effect and cross-over effect appear both very unlikely in this study. Should normality be not adequate, non-parametric test such as the Wilcoxon signed ranks test will be applied [20]. An appropriate generalized linear model will be used to investigate the relationship between the CSOR cross-over difference and the candidate covariates. Should any raw CSOR observations be missing (e.g. NIRS instrument failed to measure or to save measurements), their estimation via imputation or other appropriate methods will be taken into account. The comparison of growth variables by randomized arm will be performed with either the two-tailed t-test or a non-parametric alternative (e.g. Mann–Whitney test), should the normality assumption be not reasonable. The time from randomization till achievement of the full enteral feeding will be analysed with the Kaplan-Meier estimator, in which full enteral feeding as defined in the protocol will be considered as the sole ‘event’, while censoring will occur for withdrawal for any cause. Standard errors will be computed according to Greenwood formula and the log-rank test will be used for univariate comparisons.

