### Aims of the study

Primary aim of this study:

1. To evaluate the changes in the intestinal perfusion and oximetry determined by feeding in VLBW infants fed by 3 hours nasogastric nutrition (CN) *versus* infants fed by bolus nutrition (BN).

Secondary aims of the study:

2. To compare if changes in the intestinal perfusion and oximetry induced by feeding are different between IUGR and NON-IUGR infants.

3. To compare growth and nutritional status of the 2 groups by randomized arm.

4. To test if changes in intestinal oximetry and perfusion can be reliable predictors of feeding intolerance (days necessary to achieve full enteral feeding)*.*

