### Endpoints

The endpoint for the primary aim will be the cross-over difference of CSOR values, measured with NIRS before and at the end of the randomized feeds.

Aims 1 to 4 will be pursued analysing the following endpoints:

· The cross-over difference of CSOR values and of rSO2s values (i.e. the splanchnic saturation slope) in IUGR and non-IUGR infants.

· Growth and nutritional status will be measured by weight, length and head circumference. Main comparison will be between measures at randomization and at achievement of full enteral feeding. The growth at 28 days of life and at 36 weeks of gestational age will also be compared with the appropriate standard growth curves.

· The difference in the CSOR values pre- and post- feeding will be compared with the baseline CSOR value and the baseline Doppler flow velocimetry (both measured within the first 72 hours of life)*.*

· Comparison of the time needed to reach full enteral feeding (i.e. days from randomization till enteral intake of 160 ml/kg/day of formula or fortified human milk) by randomized arm;

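### The IUGR comparison for aim 2 uses the CSOR cross-over difference, so it tests only whether the bolus-continuous contrast depends on IUGR and misses an IUGR effect common to both feeds

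*Protocol article*

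**What the plan says.** Under Aims of the study, the second aim reads: "To compare if changes in the intestinal perfusion and oximetry induced by feeding are different between IUGR and NON-IUGR infants". Feeding mode is not mentioned in it. The Discussion, in the abstract and in the main text, repeats the question separately from the question of how the regimen acts.

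The Statistical analysis section defines the effect of a feed within that feed: "The impact on intestinal perfusion is defined as the difference between pre- and post-prandial CSOR values measured with NIRS 30 minutes before feeding", set against the value at the expected post-feed peak. It then moves to the within-infant contrast of the two feeds: "each infant will be evaluated both for CN and BN and the cross-over CSOR difference will be the primary endpoint".

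Three statements bear on IUGR, and for CSOR all three use that second quantity:

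- Endpoints: "The cross-over difference of CSOR values and of rSO2s values (i.e. the splanchnic saturation slope) in IUGR and non-IUGR infants".
- Statistical analysis, on the secondary comparison by IUGR status: "the cross-over difference of CSOR values as well as that of SO2s values (i.e. the splanchnic saturation slope) will be analysed comparing intra-uterine growth".
- Statistical analysis, covariate model, where IUGR status is one of the adjustment factors: "An appropriate generalized linear model will be used to investigate the relationship between the CSOR cross-over difference and the candidate covariates".

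One further item under Endpoints uses the pre-post feeding difference itself, but relates it to baseline CSOR and baseline Doppler, not to IUGR status. The other secondary analyses compare growth and time to full enteral feeding by randomized arm.

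**The concern.** The aim is about the size of the feeding response in two kinds of infant. The planned quantity is the gap between two feeding responses in the same infant. If IUGR alters both responses by the same amount, that gap does not change, and a comparison of gaps cannot show the alteration.

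IUGR status is the stratification factor and the subject of one of the article's two main questions. A null result from the planned comparison could easily be reported as showing that IUGR does not alter the response to feeding. The comparison supports only a narrower statement: no evidence that IUGR changes the contrast between bolus and continuous feeding.

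**Working it through.** **Inputs from the protocol article.** About 10 IUGR and 10 non-IUGR infants (Stratification). Two-sided alpha 0.05 and a mean pre-post CSOR change under bolus (BN) of 0.10 (Sample size). Cross-over differences of 0.07, 0.10 and 0.13 with SDs of 0.10, 0.15 and 0.20 (Table 1).

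**Assumed, not in the article.** The SD s of a single feed's change (0.10, 0.15, 0.20), the correlation r between an infant's two changes (0 or 0.5), and the IUGR effect.

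**1. The plan's own figures.** Paired t-test, n = 20, with Table 1's SD taken as the SD of the cross-over difference. Noncentrality = difference × √20 / SD.

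| SD | Difference | Noncentrality | Power computed | Power stated |
|---|---|---|---|---|
| 0.10 | 0.07 | 3.13 | 84.4% | 84% |
| 0.15 | 0.10 | 2.98 | 80.7% | 80% |
| 0.20 | 0.13 | 2.91 | 78.7% | 78% |

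Table 1 reproduces. It refers to the primary comparison; the article states no power for aim 2.

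**2. What the planned IUGR comparison estimates.** Let the mean changes in non-IUGR infants be B (bolus) and C (continuous), and in IUGR infants B + g_B and C + g_C.

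- Cross-over difference, IUGR minus non-IUGR: [(C + g_C) − (B + g_B)] − (C − B) = g_C − g_B.
- Mean of the two changes, IUGR minus non-IUGR: (g_B + g_C)/2.

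With g_B = g_C = g, the first is 0 and the second is g. This is algebra and depends on no SD or correlation. The IUGR coefficient in a model whose response is the cross-over difference is again g_C − g_B.

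**3. Simulation of an equal shift.** 20,000 trials per scenario, 10 versus 10, g = 0.07, 0.10 and 0.13, all combinations of s and r above. The planned comparison rejected in 4.6% to 5.2% of trials, which is its type I error.

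**4. An unequal effect.** Suppose the responses in non-IUGR infants are 0.07 apart, as in Table 1's first row, and IUGR abolishes both. The cross-over difference is then 0.07 in one group and 0 in the other. With an SD of 0.10 for that difference, noncentrality = 0.07 / (0.10 × √(2/10)) = 1.57 on 18 degrees of freedom, and power is about 32%.

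**5. Comparing the mean change instead.** The SD of the mean of two changes is s√((1 + r)/2). Noncentrality = 0.10 / (that SD × √(2/10)), 18 degrees of freedom, for an assumed difference of 0.10.

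| s | SD of mean, r = 0.5 | Power | SD of mean, r = 0 | Power |
|---|---|---|---|---|
| 0.10 | 0.087 | 69% | 0.071 | 85% |
| 0.15 | 0.130 | 37% | 0.106 | 51% |
| 0.20 | 0.173 | 23% | 0.141 | 32% |

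The SD of the cross-over difference is s√(2(1 − r)). At r = 0.5 it equals s, so the left-hand power column is consistent with Table 1. At r = 0 and s = 0.10 it is 0.141, which would give about 56% power for Table 1's first row rather than the stated 84%. The right-hand power column is therefore an upper range and does not match Table 1.

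**The case against.** **Aim 2 may mean the interaction.** It follows an aim about continuous versus bolus feeding, and Endpoints says the aims will be pursued through the cross-over difference. On that reading the planned test is right. The reading is possible, but neither the aim nor the Discussion mentions feeding mode when posing the IUGR question, and the Discussion lists it beside the regimen question as a second one. The wording favours the feeding response itself.

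**Some text may allow a per-feed analysis.** The oximetry quantity is glossed as a saturation slope, which could mean a change within one feed, and the multivariable paragraph speaks of impact, a term defined per feed. For rSO2s the ambiguity stands. For CSOR it does not, because the response of the covariate model is named.

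**Stronger readings that the article does not support.**

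- A reader might infer that the planned test is blind to any IUGR effect. It is blind only to an equal shift; step 4 gives about 32% power in one unequal case.
- A reader might infer that a well-powered test is being passed over. That holds only at the smallest Table 1 SD.
- A reader might infer that the planned contrast removes exactly the Discussion's hypothesis. That hypothesis describes a perfusion state that may be present in IUGR infants. A pure difference in resting level would cancel in any pre-post change, including the one proposed here.

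**Proportion.** This is a secondary aim in a study that describes itself as exploratory. That limits the weight of the point but does not remove it.

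**Conclusion.** The point holds for CSOR. The endpoint, the secondary analysis and the covariate model all use the cross-over difference, so none estimates the difference in feeding response that aim 2 names. This is a mismatch between a stated aim and a stated analysis, not detail left to another document.

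Under an IUGR effect equal on both feeds, the expected contrast is exactly zero and the rejection rate is about 5%, whatever the SD or correlation. Under unequal effects some power remains. The power figures for the alternative rest on the assumed difference of 0.10 and on the assumed per-feed SDs and correlations.

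The planned comparison is valid as a test of interaction, and the primary analysis is untouched. It should be fixed, but it does not threaten the trial's main result.

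**What to change.** For aim 2, add a comparison between IUGR and non-IUGR infants of each infant's mean of the bolus and continuous pre-post changes, in CSOR and in rSO2s. Extend it to the superior mesenteric artery velocities where values before and after the feed are recorded; the article says only that Doppler is done alongside the oximetry and gives no exact times. Equivalently, fit a mixed model to the per-feed changes with IUGR status, modality, their interaction and period.

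Keep the planned comparison of the cross-over difference and label it the modality-by-IUGR interaction. State in the text whether the saturation slope is a within-feed change or a contrast of two changes.

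Given the power range, report the added comparison as an estimate with a confidence interval, so that a non-significant result is not read as no difference. The cost is one extra contrast and a few sentences; the CSOR and rSO2s measurements are already planned.
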